#### Passive digital phenotyping data collection

2.5.1

Fitbit devices continuously and passively collect objective data. Sleep metrics, including total sleep time, total awake time, sleep onset latency, sleep efficiency, and duration of sleep stage (light, deep, and REM sleep), are generated daily. Sleep stages are estimated using the Fitbit algorithm, based on a combination of movement and heart rate variability (HRV) patterns. Inactivity for approximately one hour is assumed to indicate sleep, while significant movements is interpreted as wakefulness. Total sleep time is calculated by subtracting the total awake time from the total inactive time.

The devices also collect physiological data, including continuous heart rate data (sampled at 5-minute intervals) and activity data, such as step counts and walking distance. Raw heart rate data will be utilized for cosinor analysis to derive circadian rhythm parameters. Step counts and walking distance, which are recorded as cumulative values, will be used to characterize circadian activity patterns. The data is automatically and wirelessly transmitted from the wearable device to the smartphone application and securely uploaded to a cloud-based research server.

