The raw, continuous heart rate data collected at 5-minute intervals will be a critical component for understanding circadian rhythmicity and autonomic function. We will apply cosinor analysis to these data, similar to the method used for step counts, to extract key rhythm parameters. Specifically, we will derive the MESOR, amplitude, and acrophase of the heart rate rhythm over a 72-hour window. The MESOR of the heart rate rhythm reflects the average heart rate, whereas the amplitude provides a measure of the magnitude of diurnal heart rate fluctuation, which can be an indicator of autonomic nervous system activity. The acrophase of the heart rate rhythm indicates the time of day when the heart rate is at its peak and is a key metric for assessing the phase of the circadian clock. These features will also be calculated separately for weekdays and weekends to account for differences in daily routines and their impact on physiological rhythms. Additionally, heart rate data collected during sleep will be used to derive the resting heart rate (RHR) as a proxy for autonomic nervous system activity, a measure known to be associated with arousal and stress. Heart rate data collected every 5 minutes from the Fitbit Inspire 3 were used to evaluate circadian rhythmicity and autonomic function. Because the device provides pulse rate variability derived from photoplethysmography(PPG) rather than true ECG based HRV, short term beat to beat analyses were not performed. Instead, resting heart rate during sleep and cosinor rhythm parameters were used to indirectly assess long term autonomic patterns. This approach allows for the characterization of autonomic rhythms in real world conditions.

Self-reported data collected via the SOMDAY application will undergo specific processing to reflect the differential impact of behavior on circadian regulation. A time-of-day weighted scoring system will be applied to substances such as alcohol and caffeine, based on their intake time (morning, afternoon, or night). For example, the disruptive potential of caffeine on sleep will be weighted more heavily for intake closer to bedtime. Similarly, stress levels and nap durations will be processed with weights to reflect their influence on circadian rhythms, a key focus of this study.

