#### Specialized analyses

2.8.7

*fNIRS data analysis*: Neuroimaging data analysis will follow established protocols using HOMER2/3 software. Statistical parametric mapping identifies task-related activation patterns, whereas functional connectivity analysis utilizes correlation and coherence measures. Group comparisons will be performed using general linear models with multiple comparison correction.

*Genomic data analysis*: Polygenic risk scores will be analyzed using linear models and population stratification controls. Gene expression data will employ differential expression analysis with multiple testing corrections. Pathway analysis using Gene Set Enrichment Analysis (GSEA) will identify biological mechanisms.

*Circadian analysis*: Cosinor analysis of physiological time series will employ nonlinear least-squares fitting to extract rhythm parameters. Population-mean cosinor analysis will test group-level rhythm differences, whereas individual cosinor analysis will characterize personal circadian profiles.

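### The acrophase of raw free-living heart rate is described as a measure of circadian-clock phase, but it also moves with the sleep/wake schedule, so a late routine cannot be told from a late clock

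*Protocol article*

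**What the plan says.** The Passive digital phenotyping section (2.5.1) sets the input: "Raw heart rate data will be utilized for cosinor analysis to derive circadian rhythm parameters". The participant wears the device through four weeks of ordinary life.

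Section 2.5.3 gives the model: "We will apply cosinor analysis to these data, similar to the method used for step counts, to extract key rhythm parameters". It continues: "we will derive the MESOR, amplitude, and acrophase of the heart rate rhythm over a 72-hour window". Steps have a cosinor of their own. They do not enter the heart-rate fit, and neither does sleep/wake state.

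The same section then interprets the parameters:

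- The acrophase, with no qualifier, "is a key metric for assessing the phase of the circadian clock".
- For amplitude the wording is softer: "the amplitude provides a measure of the magnitude of diurnal heart rate fluctuation, which can be an indicator of autonomic nervous system activity".
- On autonomic function: "resting heart rate during sleep and cosinor rhythm parameters were used to indirectly assess long term autonomic patterns".

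The only step directed at daily routine in the heart-rate analysis is a split: "These features will also be calculated separately for weekdays and weekends to account for differences in daily routines and their impact on physiological rhythms".

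Section 2.8.7 takes the parameters into inference: "Population-mean cosinor analysis will test group-level rhythm differences, whereas individual cosinor analysis will characterize personal circadian profiles". It names no activity or sleep covariate. The ANCOVA in 2.8.2 names age, sex and comorbid conditions. Clustering in 2.8.4 uses the standardized digital features.

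**The concern.** Heart rate is higher when a person is awake and moving. A single 24-hour cosine fitted to raw heart rate absorbs that wake-locked rise together with any endogenous rhythm, and the fitted peak is a compromise between the two. Someone with an ordinary clock who goes to bed and gets up late will show a late acrophase.

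The label given to the result is what is at stake. If the two groups, or two clusters, keep different hours, the difference would be reported as a difference in clock phase. The Discussion names circadian rhythm disruption among the subtypes that tailored treatment would need to recognise, so a schedule difference could be presented as a biological subtype.

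This is not a detail that a statistical analysis plan would settle. The article itself assigns the clock meaning to the unadjusted parameter.

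**Working it through.** The article states no figure here, so there is none to reproduce. The check asks how far the acrophase moves when only the schedule moves.

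**From the article:** raw heart rate, 5-minute sampling, a 72-hour window, and a cosinor with no behavioural term.

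**Assumed, not in the article:** clock component with amplitude A = 2, 4 or 6 bpm and a fixed peak at 16:00; waking adds W = 4, 8 or 12 bpm; 16 hours awake, either 07–23 or 09–01; steps in 35% of waking epochs with mean 150 steps, at 0.08 bpm per step; noise SD 5 bpm.

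**Closed form.** Steps add on average 0.35 × 150 × 0.08 = 4.2 bpm while awake. A 16-hour block of height W + 4.2 has a 24-hour harmonic of amplitude

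B = (2/π) × sin(π × 16/24) × (W + 4.2) = 0.551 × (W + 4.2),

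peaking at mid-wake: 15:00 on the early schedule and 17:00 on the late one. Each lies 1 hour (15°) from the clock peak. With

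δ = arctan[A sin 15° / (B + A cos 15°)] / 15° (in hours),

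the fitted acrophase is 15 + δ (early) or 17 − δ (late), so the shift is 2 − 2δ.

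| A | W | B | δ (h) | Shift, formula (h) | Shift, simulation (h) |
|---|---|---|---|---|---|
| 6 | 4 | 4.52 | 0.57 | 0.86 | 15.55 to 16.41 = 0.86 |
| 4 | 8 | 6.73 | 0.37 | 1.26 | 15.33 to 16.60 = 1.27 |
| 2 | 12 | 8.93 | 0.18 | 1.64 | 15.15 to 16.80 = 1.65 |

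The simulation used 400 replicates per setting; these rows are the smallest, middle and largest shifts of the grid. A second set of assumptions (clock peak 15:00, A 3–8, W 5–15, noise SD 4) gave 0.61 to 1.55 hours. The overall range is roughly 0.6 to 1.7 hours.

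**Why the fit cannot separate the two.** If clock and schedule both move by x hours, the acrophase moves by x. A shift of 1.26 hours is therefore what one sees when both move by 1.26 hours, and also (A = 4, W = 8) when the schedule moves by 2 hours and the clock not at all.

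**Lower activity.** Halving steps reduces B by 0.551 × 2.1 = 1.16 bpm. In the simulation the amplitude fell by about 1.1 to 1.2 bpm (8% to 18%), and the acrophase changed by at most 0.09 hours, about 5 minutes.

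**Does adjustment solve it?** With perfectly known wake state and steps in the fit, the peak returned to 15.95–16.07 hours and the amplitude to its true value within about 0.05 bpm. That follows from how the data were generated. Under the second set of assumptions, steps alone left 0.49 to 1.46 hours of spurious shift. Coding still wakefulness in bed as sleep (an assumed 1.5 hours in the evening and 1 hour in the morning) left the following:

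| A | W | Unadjusted shift (h) | Adjusted shift (h) | Adjusted amplitude (bpm) |
|---|---|---|---|---|
| 3 | 10 | 1.48 | 1.14 | 6.6 |
| 5 | 10 | 1.22 | 0.84 | 8.6 |
| 8 | 5 | 0.73 | 0.36 | 9.8 |
| 3 | 15 | 1.54 | 1.27 | 8.4 |

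With a milder error (1 hour of waking coded as sleep per day) the residual shift was 0.1 to 0.7 hours. With correct coding but a gradual wake effect (2-hour time constant) it was 0.25 to 1.34 hours. Adjustment reduces the problem but does not yield clock phase.

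**The case against.** The strongest case is that an unadjusted cosinor is a legitimate descriptive feature in exploratory phenotyping, and that covariate modelling is ordinarily left to fuller documents. Several safeguards also exist: shift workers and people with irregular schedules are excluded (2.2); weekdays and weekends are analysed apart; step-based cosinor, L5, M10, IS and IV are derived alongside, so the behavioural rhythm is visible in the same feature set; and late sleepers may well have late clocks.

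Part of this stands. As a descriptor the feature is sound. But the exclusions leave stable late schedules eligible, and someone who is routinely late is late on weekdays and weekends alike. Having step features in the same set does not change what the heart-rate acrophase is said to mean. If late schedules and late clocks go together, the acrophase still cannot show which is present. The limitations in the Discussion mention 5-minute sampling and photoplethysmography, but not this.

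A reader might go further and infer that low activity will appear as a clock abnormality. The working does not support that: activity acts on amplitude. A reader might also charge the article with misreading amplitude as autonomic function. Its wording there is conditional and indirect, and resting heart rate during sleep is derived as a second proxy that walking affects less.

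**Conclusion.** The point holds for the acrophase. The article gives it an unqualified clock-phase meaning that raw free-living heart rate cannot support. A schedule 2 hours later with an unchanged clock moves it by roughly 0.6 to 1.7 hours. The size rests entirely on assumed clock, wake and step effects. The direction needs only that waking raises heart rate.

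Two limits apply. The article gives no group figures for bedtime, rise time or activity, so bias in the actual comparison is possible but not shown. Nor do the documents support making an adjusted fit the sole input to group tests and clustering. Section 2.5.1 says that about an hour of inactivity is taken as sleep, so lying awake in bed may be scored as sleep. That is likely more common in insomnia, and the error could then differ between the groups. The matter is worth correcting, mainly because of what the study may conclude.

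**What to change.** In 2.5.3 and 2.8.7:

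1. Describe heart-rate acrophase and amplitude as features of the 24-hour behavioural and physiological rhythm, and delete the statement that acrophase assesses clock phase.
2. State that no group difference or cluster will be labelled circadian misalignment on unadjusted heart-rate acrophase alone.
3. Add a sensitivity fit of the heart-rate cosinor with concurrent steps (differenced, because they are stored as cumulative values) and device sleep/wake state. Report it beside the unadjusted values, as less confounded and not as clock phase.

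Item 3 applies where these series exist at epoch level. Section 2.5.1 lists sleep metrics generated daily and does not state the time resolution of steps or sleep state, so this must be confirmed first.

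The cost is rewording plus one further analysis; data collection is complete and no new data are needed. The downside is wider uncertainty (in one set of simulations the SD of the acrophase rose from 0.19 to as much as 0.37 hours) and residual bias that may differ between groups. The report should say so.

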#### Data adherence and privacy

2.5.4

The integration of the SOMDAY application with the Fitbit platform enables automatic synchronization of both active and passive data, allowing the research team to monitor participant compliance in real time. This system also allows participants to view their daily summaries, such as sleep and activity data, directly within the SOMDAY interface, thereby increasing self-awareness and motivation to adhere to the study protocol. In addition, an automated notification system sends encouragement messages when adherence for either data type falls below 50% within a given week, which further helps reduce participant fatigue and dropout. To ensure data security, all information collected through the SOMDAY application and Fitbit platform was encrypted during transmission and stored on an independent, access-restricted server maintained by the research team. Database encryption key management was implemented to prevent key leakage and unauthorized access. User access rights and activity logs were continuously monitored, and sensitive data were encrypted to prevent the exposure of personal identifiers.

### Functional near-infrared spectroscopy neuroimaging

2.6

Prefrontal cortex activity is assessed using functional near-infrared spectroscopy (fNIRS), a non-invasive neuroimaging technique that measures hemodynamic responses associated with neural activation. fNIRS was selected because of its advantages in studying sleep disorders, including tolerance to head movement, silent operation, and suitability for participants who may have difficulty with traditional neuroimaging modalities.

#### fNIRS system and setup

2.6.1

A portable multichannel fNIRS device (NIRSIT, OBELAB Inc., Seoul, Republic of Korea) is used to record the prefrontal hemodynamic responses. The system employs near-infrared light at dual wavelengths (760 and 850 nm) to measure the changes in oxygenated (HbO_2_) and deoxygenated (HbR) hemoglobin concentrations. The device features a flexible probe configuration optimized for prefrontal cortex coverage with source-detector separations of 30 mm to ensure adequate cortical sensitivity.

All fNIRS assessments are conducted at the Korea University Anam Hospital by trained research personnel, following standardized protocols. The session room maintained at a comfortable temperature and lighting conditions to minimize environmental confounding factors. The participants are seated comfortably with the fNIRS cap positioned according to the international 10–20 system, ensuring consistent probe placement across participants.

#### Experimental protocol

2.6.2

The fNIRS assessment protocol consist of approximately 25 minutes of recording and structured as follows.

*Pre-task resting state (5 minutes)*: Participants maintain a relaxed state with their eyes open, fixating on a neutral stimulus (white cross on black background) to establish baseline prefrontal activity and functional connectivity patterns.

*Cognitive task battery (15 minutes)*: Two validated cognitive tasks are administered to probe distinct aspects of prefrontal function:

*Visuospatial N-back task (8 minutes)*: This task assessed spatial working memory capacity, a cognitive domain frequently impaired in insomnia. Participants view a sequence of visual stimuli (stars) appearing at different locations in an 8-grid layout. They are required to respond when the current stimulus position matched the position from one, two, or three trials back (1-back, 2-back, 3-back conditions). Each difficulty level is presented in separate blocks (2 min each), with 1-minute rest periods between blocks. The performance metrics included accuracy, reaction time, and the d-prime sensitivity index.*Stroop color-word task (7 minutes)*: This task evaluated cognitive inhibition and attentional control. Participants view color words (red, blue, green, and yellow) displayed in either congruent or incongruent colors and are instructed to respond to the ink color while ignoring the word meaning. The task included three conditions: neutral (colored symbols), congruent (word and color matches), and incongruent (word and color mismatch). Each condition is presented for 2 min, with brief interblock intervals.

*Post-task resting state (5 minutes)*: A final resting-state period with eyes closed is recorded to assess post-task recovery and compare with pre-task connectivity patterns.

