#### Outcome measures and analysis framework

2.6.4

The primary fNIRS outcome measures were designed to capture task-related activation and intrinsic functional connectivity.

*Task-evoked activation*: Hemodynamic responses during cognitive tasks will be quantified as changes in the HbO_2_ concentration relative to the pre-task baseline. Task-specific activation patterns will be calculated for each cognitive domain (working memory and cognitive inhibition) and will be compared between insomnia and control groups.

*Resting-state functional connectivity*: Functional connectivity will be assessed by calculating Pearson correlations between HbO_2_ time series from different prefrontal regions during both pre- and post-task resting periods. Network topology measures, including node strength and clustering coefficients, will be derived to characterize the prefrontal network organization.

*Hemispheric asymmetry indices*: Lateralization of prefrontal function will be quantified using asymmetry indices by comparing left- and right-hemisphere activation and connectivity patterns. These measures provide insight into the potential hemispheric imbalance associated with insomnia.

*Cognitive performance-brain activity relationships*: Correlations between behavioral performance measures (accuracy, reaction time) and concurrent brain activation will be calculated to examine brain-behavior relationships and identify potential compensatory mechanisms in insomnia.

The fNIRS protocol will be specifically designed to be integrated with a broader deep phenotyping framework, with derived neural metrics to serve as features in computational analyses alongside clinical, digital, and genomic data to identify neurophysiological correlates of insomnia phenotypes.

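### Resting fNIRS is eyes open before the tasks and eyes closed after them, so the within-participant pre/post connectivity difference cannot be read as post-task recovery

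*Protocol article*

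**What the plan says.** Section 2.6.2 (Experimental protocol) describes one sequence of about 25 minutes: 5 minutes of rest, 15 minutes of tasks, 5 minutes of rest.

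- Before the tasks: "Participants maintain a relaxed state with their eyes open, fixating on a neutral stimulus". The stated purpose is "to establish baseline prefrontal activity and functional connectivity patterns".
- After the tasks: "A final resting-state period with eyes closed is recorded to assess post-task recovery and compare with pre-task connectivity patterns".

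Section 2.6.4 (Outcome measures and analysis framework) opens with "The primary fNIRS outcome measures were designed to capture task-related activation and intrinsic functional connectivity". It then computes Pearson correlations between HbO2 "time series from different prefrontal regions during both pre- and post-task resting periods". The same section quantifies task-evoked activation as a change in HbO2 "concentration relative to the pre-task baseline", and says that derived neural metrics will serve as features in the multimodal analyses.

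The article describes no eyes-closed rest before the tasks, no eyes-open rest after them, no counterbalancing and no treatment of eye state in the analysis. The fNIRS limitations in the Discussion cover spatial resolution and prefrontal-only coverage, but not eye state.

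**The concern.** A recovery comparison needs two rest periods that differ only in whether the tasks have been done. Here they also differ in eye state, in the same direction for everyone. A change in connectivity from the first rest to the second could come from the tasks, from elapsed time, from closing the eyes, or from any mixture of these.

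At stake is the meaning of a result from a primary fNIRS outcome. A pre/post change could be published as prefrontal recovery when it is partly or wholly a response to eye closure. If the change were also compared between groups, a different response to five minutes of eyes-closed rest in people selected for sleep difficulty could be reported as altered recovery in insomnia. If a change score entered the multimodal models, the wrong label would shape how a subtype or predictor is interpreted.

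**Working it through.** No sample size, power or alpha figure is involved, so the check is one of identifiability.

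**Session timing, to confirm the sequence.** N-back: 3 × 2 + 2 × 1 = 8 min. Stroop: 3 × 2 = 6 min plus brief intervals, stated as 7 min. Battery: 8 + 7 = 15 min. Session: 5 + 15 + 5 = 25 min. The article's figures agree with one another.

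**Model.** Let g = 1 for insomnia and 0 for controls, p = 1 for post-task and 0 for pre-task, e = 1 for eyes closed and 0 for eyes open. Write mean connectivity as

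b0 + b1·g + b2·p + b3·e + b4·g·p + b5·g·e.

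Here b2 is the task/time effect in controls (the intended recovery effect), b3 is the eye-closure effect in controls, and b4 and b5 are the group differences in each. Section 2.6.2 sets e = p in every recorded cell, which gives:

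| Cell | p | e | Mean |
|---|---|---|---|
| Control, pre | 0 | 0 | b0 |
| Control, post | 1 | 1 | b0 + b2 + b3 |
| Insomnia, pre | 0 | 0 | b0 + b1 |
| Insomnia, post | 1 | 1 | b0 + b1 + b2 + b3 + b4 + b5 |

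**What can be estimated.**

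1. Pre/post change in controls: b2 + b3. In the insomnia group: b2 + b3 + b4 + b5. The correlation of p and e is 1.0, and the matrix with columns (1, p, e) has rank 2 of 3. Neither b2 nor b3 is estimable alone.
2. Group difference in change: b4 + b5. A common eye-closure effect b3 cancels, but b5 does not. The full matrix has rank 4 of 6, and b4 is not estimable unless b5 = 0 is assumed. Under that assumption it is.
3. Group difference at pre-task rest: b1. At post-task rest: b1 + b4 + b5. Both are estimable, because eye state is the same for both groups within each period. The second is a difference in the eyes-closed, post-task state. It does not say how much is due to the tasks and how much to eye closure.
4. Task-evoked activation is referred to the eyes-open pre-task period and does not use the eyes-closed rest.

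**What design would have identified it.** With the same eye state in both periods, the group-by-period model has rank 4 of 4. With both eye states in each period, the six-parameter model has rank 6 of 6 and b2 is estimable apart from b3. The article states that data collection is complete, so neither can be added now.

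**Size.** For any observed change D in controls, b2 = D − b3, and every value of b3 fits the data equally well. The documents give no value or range for b3 or b5, so neither the amount nor the direction of bias can be calculated.

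**The case against.** The case on the other side has several parts.

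- **Unstated analyses.** The article does not define a post-minus-pre score or a between-group test of change. It says only that the post-task period is for assessing recovery and for comparison with pre-task connectivity, and that connectivity is computed "during both pre- and post-task resting periods". This stands for the group test, which is treated here as conditional. It does not remove the stated pre/post comparison or its recovery reading.
- **Cancellation between groups.** Eye state is the same for both groups in each period, so a shared effect drops out of a group-by-period contrast. This stands. What remains is a differential response to eye closure. The article offers no evidence of one, but also none for its absence, and it names physiological hyperarousal as a feature of some insomnia subtypes.
- **Limited reach.** The first objective in Section 2.8 is insomnia versus control, which is sound within either rest period. Section 2.8.4 clusters on digital phenotyping features, and no recovery feature is named for the multimodal models. This stands and limits the consequence to one interpretation.
- **A fuller protocol or SAP could deal with it.** This does not stand. Both eye states and the intended comparison are written in the article, and no analysis can supply cells that were not recorded.

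A reader might go further and infer that all resting-state results, or all topology and asymmetry measures, are invalid. The documents do not support that. Section 2.6.4 describes no topology change score, and its asymmetry indices compare left with right hemisphere, not before with after. Such measures would share the problem only if formed as pre/post differences.

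**Conclusion.** The point holds for the within-participant comparison in Section 2.6.2: the recovery effect is completely aliased with eye state and is not identifiable at any sample size. This rests only on the two stated eye states and on there being no other rest recording than the article describes.

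For a between-group comparison of the change, the problem is conditional. The result can be read as differential recovery only on the assumption that eye closure affects both groups equally. A reader might infer that the group contrast is confounded in the same unconditional way, but that overstates it, because a common effect cancels.

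Within-period group comparisons and task-evoked activation are untouched. The size of any bias is unknown. The matter should be corrected before the fNIRS results are interpreted, but it does not threaten the study's main aims.

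**What to change.** 1. Withdraw the recovery interpretation in Section 2.6.2, or relabel the pre/post connectivity difference as a combined task/time-plus-eye-state change.
2. In Section 2.6.4, treat eyes-open pre-task rest and eyes-closed post-task rest as two separate states, each compared between groups.
3. Carry only within-state connectivity features into the multimodal models.
4. If a group comparison of the change is reported, state beside it the assumption that eye closure acts equally in both groups.
5. Add the eye-state difference to the fNIRS limitations in the Discussion.

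The 1-minute rests between N-back blocks should not be used as a substitute recovery measure. There are only two, each one-fifth the length of a resting period. Their eye state is not stated. They lie within the N-back task, so they cannot show recovery from the whole 15-minute battery.

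The cost is wording, feature labels and one exploratory claim. No new data are needed, and the fNIRS outcome analyses are still written in the future tense.
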